#### Mixed Methods Analyses

Qualitative feedback, individual participant response to treatment, and treatment implementation measures from the case series will be interpreted together to elucidate the association between how experiences and perceptions of U-PEACE vary by treatment outcome and implementation. This information will be used to modify U-PEACE before the implementation of the RCT. RQA [89,90,95] will be used to quickly and efficiently summarize qualitative feedback from participants and community members throughout the trial. A joint display analysis will be developed following best practices [96]. The joint display will simultaneously illustrate individual quantitative (eg, emotion regulation, diagnostic symptomatology such as depression and anxiety, and culturally relevant outcomes such as experiences of discrimination) and qualitative (eg, themes and quotes) results reflecting participants’ experiences of U-PEACE. Likewise, we will simultaneously examine quantitative (eg, fidelity) and qualitative (eg, themes) implementation data to guide protocol changes before the RCT; these changes will be aimed to increase U-PEACE feasibility and appropriateness.

For the RCT, patterns in the quantitative outcome and implementation data will be examined to generate specific questions for the qualitative interviews after the RCT. Multilevel modeling will be used to elucidate treatment response classifications and will be used to ensure an appropriate representation of adolescent and caregiver participation in the interviews. The resulting joint display will compare representative interview quotes across key domains (eg, intervention acceptability and tolerability) and implementation indicators (eg, U-PEACE fidelity and alliance) between those classified into 2 aggregated clusters: nonresponders, which consists of those identified as falling within the deteriorated or unchanged categories, versus responders, which will include participants whose scores fall within the improved or recovered categories. Inclusion of implementation outcomes (ie, fidelity to treatment, treatment adherence, and acceptability) will provide insight into the sustainability of U-PEACE in diverse high school settings.

#### Sample Size and Power Analysis

The recommended size for a single focus group is 6 to 8 participants for sufficient diversity of opinions and to encourage discussion [97,98]. Consequently, we will seek to have at least 5 participants included in each adolescent, caregiver, teacher, school administrator, and school mental health provider focus group, for 25 participants at the initial adaptation phase, to gather sufficient data to inform the modifications to the UP-A (aim 1), rather than powering for specific effects. In addition, qualitative feedback will be obtained following the pilot case series and RCT (aims 2 and 3) to inform implementation outcomes (aim 4). All participants in the pilot case series will be invited to participant in the qualitative feedback interviews, and the same recommendation size of 25 participants will be used for the RCT qualitative feedback interviews. Power calculations for the nested multilevel models were conducted using Optimal Design 3.1 [99] to identify the minimum number of participants needed to participate in the RCT across 7 treatment groups with 5 assessment points. We estimated power using intraclass correlation coefficient (ICC) values of 0.01 based on recent effectiveness trials with a similar transdiagnostic intervention [100] and a more conservative estimate of 0.10. With an estimated sample size of 63 adolescents, the sample would have sufficient power (0.80) to detect an effect size of *d*=0.94 (ICC=0.01) or 1.21 (ICC=0.10), which are smaller effect sizes (*d*=1.25) than those observed in an UP-A RCT [43].

### Cost Analysis

While the results are expected to be preliminary and descriptive, estimates of the intervention’s total cost will be calculated. The total cost of personnel will be calculated by multiplying each personnel’s time spent on intervention activities (eg, intervention session delivery, supervision, maintenance of school engagement, and personnel travel) by their respective wages, then summing the resulting products. Administrative records of the project’s financial spending will be used to calculate nonpersonnel costs. Total costs for intervention implementation into each school will be calculated, in addition to the average cost of providing each adolescent with services. Implementation costs (cost for starting U-PEACE in schools, such as costs to initially train clinicians) will be analyzed separately from sustainability costs (cost for continuing to deliver U-PEACE in schools, such as the cost of previously trained clinicians continuing to deliver U-PEACE).

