### This Study

The purpose of this study is to iteratively adapt and implement a school-based, indicated prevention version of the UP-A in Title 1 high schools that cater to minoritized youth and evaluate its efficacy within that setting. The program will be known as the Unified Protocol for Transdiagnostic Treatment of Emotional and Academic Challenges in Education (U-PEACE). First, we anticipate that verbal feedback from community members would suggest that U-PEACE is a good fit for Title 1 high schools, with the inclusion of some suggested modifications. Next, we anticipate that U-PEACE, developed via an iterative feedback process, including 3 phases of evaluation (ie, qualitative interviews of stakeholders, pilot case series, and an RCT), will lead to reductions in anxiety and depression symptoms, as well as improvements in academic domains (eg, grades and attendance). Finally, we anticipate that adoption of U-PEACE will be more cost-effective for high schools than services as usual (SAU) within integrated school health clinics.

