**Figure 2 figure2:**
[figure not shown]
Anticipated CONSORT (Consolidated Standards of Reporting Trials) diagram for the Unified Protocol for Transdiagnostic Treatment of Emotional and Academic Challenges in Education (U-PEACE) study. The diagram includes information from the anticipated participant allocation. At the completion of the study, a final CONSORT diagram will be presented with study results that include final data regarding recruitment and retention of participants. SAU: service as usual.

While the research team will be exploring the feasibility of telehealth-delivered U-PEACE, most U-PEACE sessions are expected to be delivered in person, during lunchtime, and in group format. Students who are enrolled in U-PEACE will be permitted to access additional primary, medical, and mental health care services within the school clinics throughout their participation in U-PEACE. The original UP-A typically takes place over 12 to 16 sessions. Thus, it was anticipated that U-PEACE would eventually contain a session count in this range. Each U-PEACE group will ideally have approximately 4 to 8 students enrolled in it at one time, as well as 1 to 2 clinicians in training who serve as program leaders for the group. At the beginning of the U-PEACE group, adolescent participants will receive a binder of U-PEACE session and homework worksheets that they can reference when learning and reviewing the program content. Adolescents will be expected to bring their binders to every U-PEACE session and practice skills learned in the group as homework between program sessions. In addition to U-PEACE binders, adolescents will also be given a caregiver session summary sheet to provide to their caregivers; these summary sheets are intended to keep caregivers informed about skills their adolescents are learning in U-PEACE.

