Although initial community member feedback suggested that the research team bring external clinicians into the schools to deliver U-PEACE, the team decided to also incorporate nonclinic school staff into the delivery of U-PEACE by adding coaches to the program. Coaches were typically existent school counselors or school mental health providers at the target schools who are intended to function in U-PEACE in a similar manner to how caregivers function in the UP-A: their primary role is to review and practice skills learned in U-PEACE sessions with adolescents outside of the program (eg, ensuring homework completion). Coaches will try to meet with each assigned student one time per week for approximately 15 minutes. During the meeting, coaches will briefly check in with students regarding whether they have been able to practice the skills they learned in session. They will also provide students with session summary materials if they cannot attend the previous session.

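### U-PEACE leader time is priced only at the wages of the trial's trainee clinicians, so the cost figures may not carry over to a school that adopts the program

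*Protocol article*

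**What the plan says.** All places are in the protocol article.

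- **Pricing rule (Cost Analysis).** Each person's time on intervention activities is multiplied "by their respective wages, then summing the resulting products". The activities given as examples are "intervention session delivery, supervision, maintenance of school engagement, and personnel travel". Nonpersonnel costs come from the project's spending records. The outputs are a total per school and an average per adolescent, and the results are labelled preliminary and descriptive.
- **Start-up and recurring cost (Cost Analysis).** Implementation cost is the "cost for starting U-PEACE in schools, such as costs to initially train clinicians". Sustainability cost is illustrated by "the cost of previously trained clinicians continuing to deliver U-PEACE". The two are analyzed separately.
- **Who delivers (Study Intervention).** Each group has "1 to 2 clinicians in training who serve as program leaders for the group". Early community feedback was that "the research team bring external clinicians into the schools to deliver U-PEACE", and the team then added coaches, typically existing school counselors or mental health providers. "Coaches will try to meet with each assigned student one time per week for approximately 15 minutes".
- **What the cost result is for.** The Introduction (This Study) expects that "adoption of U-PEACE will be more cost-effective for high schools than services as usual (SAU"). The Discussion (Potential Study Implications) says the cost findings can tell others what resources similar programs need. Anticipated Findings expects the adapted program to draw on resources the schools already have.

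**The concern.** The rule costs the trial as it was staffed. The stated question is what U-PEACE would cost a high school that takes it up. These are the same quantity only if an adopting school would lead its groups with clinicians in training on the same pay. The article does not say who would lead groups in such a school, or at what wage, and it describes no repricing.

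The two figures a school would budget from are the average cost per adolescent and the sustainability cost. Both contain leader time at trainee wages. A school that has to employ other staff could not read its own cost from either one.

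**Working it through.** The article states no wage, staff-hour total or cost, so there is no figure to reproduce. The checks below apply its own rule, cost = sum of (time × wage). Every dollar amount, wage ratio, session length and supervision time is an assumption.

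**1. Leader-delivery line alone.** With the same hours, the proportional shortfall against a replacement wage is 1 − (trainee wage / replacement wage).
- Ratio 0.75: 1 − 0.75 = 25%.
- Ratio 0.40: 1 − 0.40 = 60%.

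If replacement staff earn no more than trainees, there is no shortfall.

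**2. Leader and supervision cost together.** Assume a trainee wage of $20/h, a qualified leader at $40/h, a supervisor at $65/h and 13 sessions. Thirteen is the number of weekly meetings in the comparison arm and lies within the expected 12 to 16 sessions; it cancels in the ratio. With n leaders, h hours per session and s supervision hours per session:
- trial cost = 13 × (n·h·20 + s·65 + s·n·20)
- adopting school, qualified leaders without supervision = 13 × n·h·40

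| n | h | s | Trial | Adopting school | Ratio |
|---|---|---|---|---|---|
| 1 | 1 | 0 | 13 × 20 = $260 | 13 × 40 = $520 | 0.50 |
| 1 | 1 | 0.5 | 13 × (20 + 32.5 + 10) = $812.50 | $520 | 1.56 |
| 2 | 2 | 0.5 | 13 × (80 + 32.5 + 20) = $1,722.50 | 13 × 160 = $2,080 | 0.83 |
| 2 | 2 | 1 | 13 × (80 + 65 + 40) = $2,405 | $2,080 | 1.16 |

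The ratio falls on both sides of 1. If the adopting school keeps the same supervision, the difference (trial minus adopting school) is 13 × n × (h + s) × (20 − 40), which is negative whenever the trainee wage is the lower one. For the second row the adopting school would then cost 13 × (40 + 32.5 + 20) = $1,202.50, and the ratio is 812.50 / 1,202.50 = 0.68. So the sign depends on supervision as well as wages, and the article gives neither amount.

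**3. How much staff time is involved.**
- Leaders: 7 groups (Sample Size and Power Analysis, read as U-PEACE groups) × 12 to 16 sessions × 1 to 2 leaders = 84 to 224 leader-sessions.
- Coaches: 12 to 16 weekly meetings × 0.25 h = 3 to 4 hours per student. With 63 adolescents and an assumed 1:1 allocation, about 32 are in U-PEACE, which gives 96 to 128 hours.

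These are volumes and do not show bias. They do show that neither leader nor coach time is negligible.

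**4. Start-up against sustainability.** Total = start-up + recurring, so the split leaves the sum unchanged. With assumed training of $2,000 and recurring cost of $3,000, the total is $5,000 and sustainability alone is 3,000 / 5,000 = 60% of it. A reader goes wrong only by taking the sustainability figure as the full cost of adoption, or if leaders have to be replaced and their retraining is not entered there.

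**The case against.** Four stronger readings are tempting, and the other side answers each with some force.

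- **That cost to a school is understated.** Supervision, the cost that goes with using trainees, is explicitly priced. So are travel and school-engagement time, which for an external team may exceed what a school would bear. Research payments left in the spending records would also push the figure up, although nothing says they would be left in. This objection stands for total cost. It does not remove the mismatch, and the cases with ratios above 1 assume that supervision stops once qualified staff take over, which the article does not say.
- **That training is left out.** It is counted, under start-up, and separating start-up from recurring cost is ordinary practice. That trainee leaders move on and must be replaced is a reasonable inference, but it is not in the text. The sustainability example does not exclude retraining.
- **That coach time is excluded.** The activity list is only illustrative, and coaches are described as part of delivery, so their meetings fit the rule. What remains is a need for clarity: the only coach payment the article states (Ethical Considerations) is for questionnaires, so spending records would not show the meeting time.
- **That a comparison with usual services is tilted by wage level.** Cost Analysis describes costing of U-PEACE only, and no wage for usual services appears anywhere. This cannot be shown from the article.

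It can also be said that an article leaves wage sources and sensitivity analyses to the full plan, and that trainee delivery may be the intended model in university-run clinics. Both are fair. But the article does state its pricing rule and the use to be made of the result, and the point rests on those two statements. The preliminary label lowers expectations of precision; it does not make the trial's staffing the same as a school's.

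**Conclusion.** The point holds as a question of transferability. Leader time is valued only at the trial's own trainee wages, while the result is meant to inform schools that would adopt the program. The average cost per adolescent and the sustainability cost may not apply to such a school.

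The leader-delivery line is too low if replacement staff earn more than trainees, by 25% to 60% under assumed wage ratios of 0.75 to 0.40. That range does not extend to total cost. A reader might infer that total cost is understated; the article does not support this, because its direction depends on wages and supervision time that are not given and it reverses within the assumptions tried.

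Because the cost results are declared descriptive, this is a modest point. It is worth acting on because the remedy is cheap.

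**What to change.** In Cost Analysis:

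1. Keep the cost at actual wages. Add a sensitivity figure that reprices the same leader hours at the wages of the staff an adopting school would employ, and state the supervision time and cost assumed in each scenario.
2. Name coach meeting hours among the intervention activities and price them at school-staff wages.
3. Report start-up and sustainability costs separately and summed, with any retraining of replacement leaders under sustainability.

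The rule already requires leader hours, so the additions are wage rates, a record of coach meeting time and a few spreadsheet lines. The price is a little more costing work and a per-student cost that may look less favourable.

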**Methods:**

For initial adaptation, members of participating high school communities will be presented with original, unadapted intervention materials and asked to provide qualitative feedback on how to make the program more appropriate and feasible for their schools (aim 1). After initial adaptations are implemented, an open-trial pilot case series will assess the appropriateness and feasibility of the resulting program: the Unified Protocol for Emotional and Academic Challenges in Education (aim 2). Initial outcome data and qualitative feedback from pilot case series participants will then inform final adaptations for the randomized controlled trial—in which the adapted program will be compared to high schools’ mental health services as usual (aim 3). The adapted program’s effectiveness will be evaluated by using a mixed methods approach, and feasibility will be preliminarily assessed through cost-effectiveness analyses (aim 4).

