### Study Timeline and Aims

This study has 3 distinct phases to accomplish 4 primary aims using a hybrid-type 1 effectiveness-implementation design [63]. In phase 1, we will interview community members for feedback on (1) mental health needs of adolescents at the target schools and (2) suggestions for delivering transdiagnostic therapeutic services in a high school setting (aim 1). The feedback obtained will be used to inform adaptations for the first iteration (pilot case series) of U-PEACE (school-based UP-A). In phase 2, we will initiate an open-trial pilot case series study with the first iteration of U-PEACE. The pilot case series will be initiated to assess the feasibility of program implementation and identify additional implementation barriers to be remedied in the second iteration (RCT). Feedback from interviews with participants in the pilot case series and support personnel for U-PEACE implementation will be incorporated into U-PEACE’s content and delivery (aim 2). In phase 3, we will initiate a randomized, controlled effectiveness trial (RCT) in which the second iteration of U-PEACE will be compared to mental health services as usual in Title 1 high schools (aim 3). In addition, in phase 3, we will analyze U-PEACE implementation (eg, adherence to U-PEACE and session attendance), collect additional feedback through qualitative interviews with study participants who received U-PEACE, and analyze cost-effectiveness (aim 4). For a flowchart of the study timeline and aims, refer to Figure 1.

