#### Comparison Condition

Individuals assigned to the comparison condition will have access to any medical, social work, and psychotherapy services available through the school clinic to address emotional and behavioral concerns determined to be needed during the intervention period. The school clinic services are available in person or via telehealth throughout the year. A study staff member will also meet with all SAU adolescents for approximately 10 minutes per week (via telehealth as needed) for 13 weeks to complete weekly study measures, assess and provide linkage to clinic services requested or needed, and monitor for clinical deterioration. If an adolescent seems to be deteriorating in any significant way, additional mental health services or appropriate referrals will be offered after consultation. Data will also be collected from SAU participants 1-month after completion of the 13 weekly meetings. After the 1-month follow-up, SAU participants may be offered participation in the U-PEACE program via telehealth or in person.

SAUs vary in frequency and type based on the availability of the school clinic providers. These services may include weekly individual or group CBT, case management, and psychological and psychiatric consultations. These services are often provided by nurses, primary care physicians, master’s-level therapists, social workers, psychologists, or psychiatrists. The receipt of these services within the school clinic will be monitored and reported. If a higher level of care is needed than what is typically provided through the school clinic, patients are referred to community resources. Participants will also be asked to report on their access and use of emotional and behavioral health services outside of the school clinic.

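### The cost analysis as described costs U-PEACE alone, so it cannot address the stated hypothesis that U-PEACE is more cost-effective than services as usual

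*Protocol article*

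**What the plan says.** Three places in the protocol article promise a cost-effectiveness result.

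- The section This Study states a comparative expectation: "we anticipate that adoption of U-PEACE will be more cost-effective for high schools than services as usual (SAU) within integrated school health clinics".
- The Methods paragraph of the abstract says "feasibility will be preliminarily assessed through cost-effectiveness analyses (aim 4".
- Study Timeline and Aims lists, for phase 3, "and analyze cost-effectiveness (aim 4". The same section counts aim 4 among four primary aims.

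The Cost Analysis section is the only description of the economic method. Its target is the total cost of the intervention. Personnel cost is time spent on intervention activities multiplied by wages. For the rest, records of the project's "financial spending will be used to calculate nonpersonnel costs". The outputs are: "Total costs for intervention implementation into each school will be calculated, in addition to the average cost of providing each adolescent with services". Start-up costs are then separated from continuing costs, and both are defined for U-PEACE. The section calls its results preliminary and descriptive.

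Two other passages bear on what a comparison would need. Comparison Condition says of SAU clinic services: "The receipt of these services within the school clinic will be monitored and reported". Study Intervention says of the other arm: "Students who are enrolled in U-PEACE will be permitted to access additional primary, medical, and mental health care services".

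**The concern.** A claim that one programme is more cost-effective than another compares two arms on two quantities, cost and effect. The method described measures one quantity in one arm.

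The gap matters because clinic care is open to both arms. SAU students may receive weekly individual or group CBT, case management or psychiatric consultation (Comparison Condition), and U-PEACE students keep access to the school clinic. U-PEACE could replace some of that use, add to it or leave it unchanged. A gross programme cost does not show which.

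The article also says, under Potential Study Implications, that the cost findings can inform funding sources. If a U-PEACE cost per student is reported next to a favourable symptom result, under an aim labelled cost-effectiveness, readers may take it as support for the hypothesis when no comparison has been made.

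**Working it through.** The article gives no cost figure, so there is nothing to reproduce. The check is whether the described analysis produces the quantities that the hypothesis needs.

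**Quantities needed.** Per student, let P be the U-PEACE programme cost, K_U the mean cost of clinic and other services used in the U-PEACE arm, and K_S the same mean in the SAU arm. Let E_U and E_S be the mean outcomes, scored so that higher is better.

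- Cost difference: ΔC = (P + K_U) − K_S
- Effect difference: ΔE = E_U − E_S
- A way to read the two together, such as ΔC/ΔE, net benefit, or the pair (ΔC, ΔE) side by side

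**What the article plans for each.**

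| Quantity | Planned? | Where |
|---|---|---|
| P | Yes: total per school, average per adolescent, start-up and continuing costs | Cost Analysis |
| K_U | No: clinic access is permitted, but its cost is not among the listed items | Study Intervention; Cost Analysis |
| K_S | No: receipt is monitored and not valued in money | Comparison Condition; Cost Analysis |
| ΔE | Yes, through condition effects on intercept and slope in the multilevel models | Quantitative Analyses |
| ΔC joined to ΔE | No | none |

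**Consequence.** From the formula, ΔC < 0 exactly when K_S − K_U > P. The plan estimates P and never K_S − K_U, so the sign of ΔC is not determined. P on its own is positive by construction and carries no information about SAU. Without ΔC, the estimate of ΔE cannot be turned into a statement about cost-effectiveness, whatever its value.

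**Could the comparison be made from data collected?** In part. Table 2 gives the Service Utilization Form to adolescents at all four time points in the RCT. Clinic receipt is monitored, and Quantitative Analyses compares use of medication and supplemental services between conditions. These are records of resource use for K_U and K_S. The article does not attach unit costs to them or bring them into the cost analysis.

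**The case against.** **The economic part is hedged.** The abstract and Cost Analysis both call it preliminary, and Quantitative Analyses lists only implementation costs among the implementation outcomes. This stands as a reason for a moderate rating. It does not close the gap: even a descriptive comparison needs a comparator cost and an effect, and the hypothesis in This Study carries no such hedge.

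**A journal article condenses.** Unit costs, the choice of ratio or net benefit, and the interval method may sit in a fuller plan, so their absence is not the finding. The finding is that the article gives its cost method in a dedicated section and that method does not match the hypothesis in the same article.

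**The average cost per adolescent could cover both arms.** Read alone, the phrase allows it. The paragraph around it speaks only of the intervention, intervention activities and U-PEACE.

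Three stronger readings are tempting, and the documents do not support them.

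- A reader might infer that the trial cannot test the hypothesis at all. Service use is recorded in both arms, so the limit lies in the analysis described and not in the data collected.
- A reader might infer that research spending will inflate the U-PEACE cost, since nonpersonnel cost comes from project records and student payments come to 50 + 25 + 50 + 50 = US $175 each (Ethical Considerations). The text names the records as a source for the intervention's cost. It does not say that participant payments will be counted.
- A reader might infer that the weekly SAU check-ins (13 × 10 = 130 minutes per student) are research contact that must be left out of the SAU cost. Comparison Condition says they also link students to services and monitor for deterioration. Any benefit they bring stays in the SAU outcomes, so leaving out their cost is debatable.

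**Conclusion.** The article contradicts itself. It states a comparative cost-effectiveness hypothesis and announces cost-effectiveness analyses, yet it describes a cost description of one arm. Of the inputs needed, the U-PEACE programme cost and the effect difference are planned. Service costs in each arm, the cost difference and its link to effect are not. Following the text as written, the hypothesis can be neither supported nor refuted.

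Severity is moderate. A hypothesis attached to a numbered aim has no analysis that can answer it, but the efficacy comparison and participant protection do not depend on it, and rewording alone would remove the contradiction. No numerical size can be given, because the article contains no cost figures. The conclusion rests on reading Cost Analysis as confined to U-PEACE, which its opening and closing sentences support.

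**What to change.** Choose one of two routes before aim 4 is reported; the article expects the remaining results to be published in 2026.

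**(a) Make the comparison.**

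- Value the service use recorded in both arms (Service Utilization Form and monitored clinic receipt) with stated unit costs for clinic providers.
- State the perspective. The hypothesis is framed for high schools, while the clinics run on local grants (Setting and Community Partnership), so the school's cost and the total cost may differ.
- In the U-PEACE arm, add delivery and coach time.
- Report the between-arm cost difference alongside the effect difference on one named outcome, with a bootstrap interval, and describe the result as preliminary.
- Show the results with and without the SAU weekly check-in time.

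Cost: unit costs must be obtained for nurses, physicians, social workers, therapists, psychologists and psychiatrists, because the wages in Cost Analysis are those of staff working on the intervention. The article does not show whether the Service Utilization Form records the quantity of contacts, which needs checking first. At the planned 63 students the interval will be wide.

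**(b) Withdraw the claim.** Remove the cost-effectiveness wording from the abstract, This Study, and Study Timeline and Aims, and call aim 4 a descriptive cost analysis of U-PEACE. Cost: a few sentences of text and a more modest claim.
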